### Safety analysis

Safety analysis will be evaluated by assessing the rate of delayed diagnosis of significant intracranial findings that require intervention and will be compared between the two groups using a Pearson’s Chi-squared test. The time to CT head imaging will also be compared between two groups using a two-sample *t*-test or Wilcoxon rank sum test depending on the normality assumption.

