## Introduction

Mild traumatic brain injury (mTBI) is the most prevalent form of head trauma presenting to emergency departments (EDs) globally, accounting for over 90% of the more than 5 million cases reported annually in the United States (1). About 82% of patients with mTBI undergo computed tomography (CT) imaging in the ED to exclude intracranial hemorrhage or other serious brain injuries, particularly in patients presenting with risk factors (1–3). However, this approach has led to the routine overuse of CT scans, with up to 90% of scans returning negative results and fewer than 1% of cases necessitating neurosurgical intervention (4–7). This overutilization contributes to increased healthcare costs, prolonged ED stays, and unnecessary radiation exposure (4–8).

The substantial economic burden associated with the acute evaluation of mTBI highlights the need for more efficient diagnostic pathways. In recent years, blood-based biomarkers have emerged as promising tools to improve triage decisions in patients with suspected mTBI. Several blood-based biomarkers have been studied in the context of mTBI including glial fibrillary acidic protein (GFAP), ubiquitin carboxy-terminal hydrolase L1 (UCH-L1), S100 calcium binding protein-B (S100B) among others (9–13). However, GFAP and UCH-L1 have both showed the highest sensitivity in predicting intracranial abnormalities on CT of the head in prospective observational cohorts (9, 12, 14). GFAP, an intermediate filament protein expressed by astrocytes, rises in the bloodstream over several hours following astroglial injury (15), whereas UCH-L1, a neuronal enzyme involved in protein turnover, increases more rapidly after neuronal damage (10). These complementary temporal profiles underpin the rationale for their combined use, which has demonstrated high sensitivity and negative predictive value (NPV) for detecting intracranial lesions in mTBI patients, with strong potential for ruling out significant intracranial pathology (9, 16). Table 1 summarizes the major clinical studies involving the utility of GFAP and UCH-L1 in mTBI.

**Table 1 tab1:** Clinical studies involving the utility of GFAP and UCH-L1 in mTBI.

Study	Sample size	Population	Age	Sample type	BM	Thresholds	Sens/Spec/NPV
Bazarian et al., 2018 (12)	1,920	Suspected mTBI (GCS 14–15)	≥18 years	Serum	GFAP, UCH-L1	GFAP: 22 pg./mL; UCH-L1: 327 pg./mL	Sens: 97.3%; Spec: 36.7%; NPV: 99.5%

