## Methods and analysis

### Study objective

The BRAIN-CT trial investigates whether providing emergency-department clinicians with rapid GFAP and UCH-L1 results, via the point-of-care i-STAT TBI cartridge, changes imaging behavior in adults with mild traumatic brain injury. The primary objective (Table 2) is to compare the proportion of patients who receive a head CT scan between a biomarker-published arm and a standard-care (biomarker-blinded) arm; we hypothesize that real-time access to GFAP and UCH-L1 levels will lower the CT scan rate compared with standard management. To address this objective, we have designed a prospective, randomized, open-label, blinded-endpoint (PROBE) adaptive trial that will enroll 350 participants, randomized 1:1 to biomarker-published versus biomarker-blinded arms using permuted blocks stratified by age group, biological sex, race, and baseline Canadian CT Head Rule risk category (Supplementary Table 1). Frequent interim analyses with prespecified efficacy and futility boundaries will permit early stopping if criteria are met.

**Table 2 tab2:** Primary and secondary objectives of the BRAIN-CT trial.

Objective	Category	Objective description	Outcome measured
Primary	–	Evaluate whether real-time access to point-of-care TBI biomarker results (GFAP, UCH-L1) reduces the use of cranial CT imaging.	Proportion of patients undergoing head CT.
Secondary (clinical impact) two-arm comparisons	Clinical decision-making	Assess the impact of biomarker result access on physician decision-making for CT use.	CT imaging timing and provider rationale.
	Efficiency and cost	Determine whether biomarker use reduces ED/hospital length of stay and healthcare costs.	LOS, resource use, hospital charges. Perform a formal ICEA of biomarker testing versus standard care.
	Patient outcomes	Compare short-term outcomes between arms (neurological deterioration, readmissions, GOS, GCS).	GOS-E/GCS at 6 months and 1-year follow-up, neurological symptoms.
	Radiation exposure	Quantify radiation dose reduction per patient between arms.	Directly measure a key safety benefit.
	Disparity analysis	Identify patient subgroups (e.g., by age, injury mechanism, comorbidity) where biomarkers influence decision-making.	Stratified CT usage, subgroup analysis of impact.
	Safety monitoring	Monitor for adverse outcomes from missed injuries in biomarker-guided arm.	Adverse events, unexpected deterioration, delayed diagnoses.

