### Post-discharge follow-up

Study staff will conduct structured telephone interviews at 6 months and 12 months after the ED visit to ascertain persistent or late-presenting neurologic symptoms, unplanned healthcare utilization (ED visits, hospital readmissions, outpatient imaging), and any delayed diagnoses of intracranial injury. Future contact is approved by subjects at the time of consent. When participants cannot be reached after three call attempts, electronic health-record review and contact of designated surrogates are attempted to complete the data set. Designated surrogates are individuals determined by the subject to be their emergency contact for the study for future contact and are named at the time of informed consent.

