### Safety monitoring

All adverse events from consent through hospital discharge–neurological deterioration, unplanned neurosurgical intervention, escalation of care, or death–are recorded prospectively; serious AEs (death, life-threatening event, or event resulting in prolonged hospitalization) are reported to the IRB and sponsor within 24 h. A blinded investigator adjudicates event relatedness to study procedures. An independent Medical Monitor reviews cumulative safety data quarterly and at each interim analysis, with authority to recommend protocol modifications or early termination if predefined neurologic severe adverse events thresholds are exceeded (Table 3).

**Table 3 tab3:** SPIRIT guidelines.

Timepoint	Study period				
	Enrolment	Allocation	Post-allocation	Follow up	Close-out
	t1	t2	t3	t4	t5
Enrolment					
Eligibility screen	X				
Informed consent	X				
Baseline assessment (GCS, labs)	X				
Randomization		X			
Interventions					
Biomarker testing		X	X		
Biomarker result communicated		X (if applicable)	X		
Standard care			X		
Assessments					
Head CT (if performed)			X		
Length of stay			X		
Adverse events monitoring			X		
Outcome adjudication (blinded)			X		
6 months follow-up (phone)				X	
12 months follow-up (phone)					X

GCS, Glasgow Coma Scale; Labs, Laboratories; CT, computed tomography.

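### The safety analysis counts only delayed diagnoses that require intervention, although Table 2 and the follow-up cover delayed diagnoses without that limit

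*Protocol article*

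**What the plan says.** Three places in the protocol article deal with harm from missed injury.

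- **Table 2, Safety monitoring row (Study objective).** The objective is "Monitor for adverse outcomes from missed injuries in biomarker-guided arm" and the outcome measured is "Adverse events, unexpected deterioration, delayed diagnoses". Nothing limits the diagnoses to those needing intervention. The row names one arm, yet it sits in the block of secondary objectives headed as two-arm comparisons.
- **Post-discharge follow-up.** The telephone interviews at 6 and 12 months ascertain "any delayed diagnoses of intracranial injury", again without a limit by severity or arm.
- **Safety analysis.** Safety is evaluated by "assessing the rate of delayed diagnosis of significant intracranial findings that require intervention", and this rate "will be compared between the two groups using a Pearson’s Chi-squared test". The section gives no time window and does not define a significant finding or an intervention.

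The Safety monitoring section adds a recording window: "All adverse events from consent through hospital discharge". In Table 3 the blinded adjudication row is marked at t3 only, while the two telephone contacts are at t4 and t5.

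**The concern.** The analysed event is a subset of what Table 2 names and the interviews collect. Take a patient who is not scanned, goes home, and is later found to have a bleed that is managed without intervention. That patient has a delayed diagnosis under Table 2 and in the follow-up data, but is not an event in the Safety analysis section.

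This matters because the section on expected impact presents the trial as a test of whether CT use can fall without loss of safety. The Safety analysis section holds the only between-arm comparison of missed injury that the article sets out. Followed as written, it could report no events while the trial's own follow-up data contain late-diagnosed intracranial injuries. An analysis plan that follows Table 2 instead would contradict the Safety analysis section.

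**Working it through.** The article gives no sample size, power or expected event count for safety, so there is no stated figure to reproduce. The check asks how much the narrow definition could leave out.

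**Inputs from the article**
- Up to 350 patients randomised 1:1, so 350 / 2 = 175 per arm (Sample size justification; Study design and methods).
- The Introduction reports "up to 90% of scans returning negative results and fewer than 1% of cases necessitating neurosurgical intervention". I take 10% with a CT-visible lesion and 1% needing intervention.
- Sensitivity is 96.5% for the whole-blood test (Table 1) and 97.6% in the plasma study behind FDA clearance (Introduction).

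**Assumptions**
- Intervention means roughly neurosurgical intervention.
- Both percentages apply to all randomised patients, although the article gives the first per scan and the second per case.
- Sensitivity is the same for lesions that do and do not need intervention.
- Every false negative in the published arm is left unscanned and is later diagnosed. This makes the event counts upper limits for the given inputs.

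**Formulas**
- Expected events = N × p × (1 − sensitivity), where p is 0.10 (broad) or 0.01 (narrow).
- Chance of at least one event = 1 − [1 − p × (1 − sensitivity)]^N.

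**Results for the published arm, N = 175**

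| Definition | Sensitivity | Expected events | Chance of at least one |
|---|---|---|---|
| Any delayed diagnosis | 96.5% | 175 × 0.10 × 0.035 = 0.61 | 1 − 0.9965^175 = 46% |
| Any delayed diagnosis | 97.6% | 175 × 0.10 × 0.024 = 0.42 | 1 − 0.9976^175 = 34% |
| Requires intervention | 96.5% | 175 × 0.01 × 0.035 = 0.061 | 1 − 0.99965^175 = 6% |
| Requires intervention | 97.6% | 175 × 0.01 × 0.024 = 0.042 | 1 − 0.99976^175 = 4% |

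The narrow definition keeps 0.01 / 0.10 = 10% of the expected events.

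**Range.** With 5% to 10% CT-positive and 0.5% to 1% needing intervention, the share kept runs from 0.005 / 0.10 = 5% to 0.01 / 0.05 = 20%. With the 150 evaluable patients per arm of the sample size section, and the 10% and 1% inputs, the chance of at least one event is 30% to 41% (broad) against about 4% to 5% (narrow).

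**Limit of either definition.** Fewer than one event is expected in the published arm under both. Zero events in 175 patients would still leave a one-sided 95% upper limit of 1 − 0.05^(1/175) = 1.7%. The broader count is more informative, but it does not make the comparison a powered one.

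**The case against.** The best defence is that collecting broadly and testing a narrower, more consequential event is ordinary practice. The follow-up section lists what the interviews ascertain and does not itself name an endpoint. That is fair, and it reduces the formal conflict to Table 2 against the Safety analysis section. That conflict remains: Table 2 names delayed diagnoses as the safety outcome, and the analysis adds two undefined qualifiers.

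A second defence is that the illustration is an upper limit. A missed lesion that never leads to later imaging is not a delayed diagnosis. Lesions found late are likely to be found through symptoms, so the one-in-ten share from all patients may not apply to them. This also stands. The direction of the loss is certain, but its size is not.

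Some stronger readings are tempting, and the documents do not support them:

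- **Unequal surveillance by arm.** A reader might infer this from Table 2's mention of the biomarker-guided arm. The row sits under a two-arm heading, and the sections on in-hospital assessment, post-discharge follow-up and safety monitoring collect data without regard to arm. The phrase needs correcting but is not evidence of bias.
- **No masked adjudication of late events.** Table 3 marks adjudication only at t3, but Study design and methods says without time limit that adjudicators are masked. The schedule is incomplete on this point; it does not show that late events go unadjudicated.
- **Deterioration and readmission dropped.** Table 2 plans to compare both between arms under patient outcomes. The choice of test can be left to the analysis plan.
- **A much larger count of missed lesions.** Applying the 96.5% negative predictive value of Table 1 to unscanned patients, at a CT rate of 55%, gives 175 × 0.45 × 0.035 = 2.8. With 10% prevalence there are only 175 × 0.10 = 17.5 lesions, so 2.8 missed would mean a sensitivity near 84%. The same row of Table 1 states 96.5%, which allows at most 0.61.

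**Conclusion.** The inconsistency is real and should be corrected. The stated safety comparison leaves out delayed diagnoses that Table 2 names as an outcome and the follow-up collects. On the stated assumptions, the published arm would expect at most about 0.4 to 0.6 events under the broad definition and about 0.04 to 0.06 under the narrow one. The chance of at least one is about 34% to 46% against 4% to 6%.

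The tenfold ratio depends on reading intervention as roughly neurosurgical, which the article does not say; a broader meaning shrinks it. A reader might go further and state as fact that most collected missed injuries would be excluded. The article gives no rate of delayed diagnoses by need for intervention, so that remains an inference.

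**What to change.** - Reconcile Table 2 and the Safety analysis section. Compare every delayed diagnosis of an intracranial injury between the two arms, from randomisation to 12 months, and report the subset requiring intervention as a separate component.
- Reword the Safety monitoring row of Table 2 so that it refers to both arms.
- Mark blinded outcome adjudication at t4 and t5 in Table 3, so that the schedule visibly covers delayed diagnoses found at the 6- and 12-month contacts.

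The cost is wording in the protocol and analysis plan, plus adjudication of a small number of late events. The data are already to be collected. The drawback is that the broader count includes lesions of less clinical weight, so the components must be shown separately and not only as a total.

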### Study design and methods

The BRAIN-CT trial is a single-center prospective, randomized, open-label, blinded endpoint study conducted in the ED of Grady Memorial Hospital, a level I trauma center. After completion of initial screening, 350 adults aged 18–85 years will be randomized 1:1 to either a biomarker-published arm (real-time GFAP and UCH-L1 values released to clinicians coupled to education on biomarker data) or a biomarker-blinded arm (standard care without biomarker disclosure). The study flow chart is provided in Figure 1. Allocation uses computer-generated permuted blocks stratified by age (3 Strata: 18–30, 31–50, 51–85 years), biological sex, race (2 Strata: Black, Not Black), Glascow Coma Scale (GCS) (2 Strata: 15, 13–14) and baseline Canadian CT Head Rule risk category (3 Strata: High Risk, Medium Risk, None) to balance key factors in routine decision making. The maximum sample size remains 350 participants for the initially planned cohort. Outcome adjudicators are masked to treatment assignments. Given the pre-existing FDA-approval of the use of the TBI biomarker testing in mild-TBI, the study is deemed no more than minimal risk to participants and a data safety and monitoring board was not required. This study is registered with clinicaltrials.gov (Identifier: NCT06932588), and the study was approved by the Institutional Review Board at Emory University and the Research Oversight Committee at Grady Memorial Hospital.

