### Inclusion and exclusion criteria

The study inclusion criteria include adults aged 18–85 years old presenting with mild TBI, defined as Glasgow Coma Scale (GCS) score 13–15, within 24 h of injury and without prior head imaging for the same incident.

For definition of timing of injury, this data will be obtained from emergency medical personnel reports, witness reports, reported history from family members or companions, and information from outside facility records if the patient was transferred. If no specific time of injury was determined, the last known normal time will be used. If the last known normal time was within 24 h of presentation, the subject will be included. If the last known normal time is over 24 h, and the exact time of incidence is not available, the patient will not be included.

Key exclusion criteria include:

Subjects with penetrating head injury.History of known brain abnormality including tumor, cerebrovascular malformation, recent brain surgery (within 6 months), prior head injury (within 6 months).Need for emergent surgical intervention for brain or alternate body organ injury.Need for emergent bedside procedures for hemodynamic or orthopedic stabilization.Patients deemed high risk for decline by the provider prohibiting the 15 min delay in obtaining imaging needed for biomarker testing.Minors, pregnant women and prisoners.

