### Sample size justification

Based on preliminary data from published studies, we defined a clinically significant impact to be attained at 15% reduction in the rate of CT head imaging in the published group, assuming 70% baseline CT utilization (23). Adjusting for an alpha of 5%, a total of 300 evaluable patients will be required (150/arm) to achieve at least 80% power to reject the null hypothesis. To account for patient withdrawal (change in exam before blood draw, leaving against medical advice, etc.), we will plan to target a maximum of 350 subjects enrolled.

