### Expected impact of the proposed trial

We are currently unaware of Level I, evidence-based protocols that use blood biomarkers to guide cranial imaging after mTBI. The BRAIN-CT trial is designed to test whether a point-of-care GFAP and UCH-L1 assay, performed within 24 h of injury, can safely reduce CT utilization while maintaining clinical safety and lowering healthcare costs. Previous efforts to limit unnecessary imaging–such as the Canadian CT Head Rule–have demonstrated high sensitivity for detecting clinically significant injuries (2, 6), yet their clinical adoption has been inconsistent. Factors contributing to this include workflow variability, clinician preference, and perceived medico-legal risk (7). The BRAIN-CT trial addresses these limitations by offering an objective, rapid biochemical assessment that is integrated into routine ED workflows. Coupled with rigorous trial methodology, including randomization, blinded outcome adjudication, and cost-effectiveness analysis, BRAIN-CT is positioned to provide critical randomized data on the feasibility, safety, and clinical impact of biomarker-guided imaging decisions, helping to inform future multicenter studies and guideline development.

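### The safety comparison relies on a Pearson chi-square where fewer than two events per arm are plausible; it cannot support a conclusion that safety is maintained

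*Protocol article*

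**What the plan says.** The Safety analysis section of the protocol article fixes both the endpoint and the test. Safety is to be evaluated by "assessing the rate of delayed diagnosis of significant intracranial findings that require intervention and will be compared between the two groups", and the same sentence names the test: "compared between the two groups using a Pearson’s Chi-squared test". No exact alternative, confidence interval or margin is given for it.

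Three other places bear on the point:

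- **Event rate.** The Introduction reports "fewer than 1% of cases necessitating neurosurgical intervention" in mild TBI. The exclusion criteria also remove patients with "Need for emergent surgical intervention for brain or alternate body organ injury".
- **Numbers.** The Sample size justification is built on CT use alone: "a total of 300 evaluable patients will be required (150/arm) to achieve at least 80% power to reject the null hypothesis", and "we will plan to target a maximum of 350 subjects enrolled". Allocation is 1:1.
- **Aim.** In the Discussion (Expected impact of the proposed trial), the trial is described as testing whether the assay "can safely reduce CT utilization while maintaining clinical safety and lowering healthcare costs".

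**The concern.** The intervention works by persuading clinicians to omit some CT scans, so the harm of interest is an injury found late. Such events should be rare in this population. A Pearson test needs reasonable expected counts in every cell, and the event cells here are likely to be close to one. A test of difference is also a poor match for the aim, because failing to reject equality does not show that the arms are similarly safe.

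The harm outcome has no other between-arm inference in the article, and the Limitations section does not say that the trial can neither detect nor exclude a sizeable excess of missed injuries. An uninformative p-value could then stand beside a claim of maintained safety in a paper meant to inform guidelines.

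**Working it through.** **Inputs**

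- n per arm: 150 (evaluable, Sample size justification) and 350/2 = 175 (maximum enrolled).
- Event rate: not given for this endpoint. The Introduction's neurosurgical figure (<1%) is used as an assumed ceiling, with an assumed range of 0.1–1%.
- Two-sided α = 0.05: stated for the primary endpoint, assumed here for safety.

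The plan states no power or precision for the safety endpoint, so there is no figure of its own to reproduce.

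**1. Expected events per arm = n × rate**

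| Rate | n=150 | n=175 |
|---|---|---|
| 0.1% | 0.15 | 0.18 |
| 0.5% | 0.75 | 0.88 |
| 1% | 1.50 | 1.75 |

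The usual minimum expected count of 5 needs a rate of 5/150 = 3.3% or 5/175 = 2.9%, about three times the assumed ceiling.

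**2. Chance that the statistic cannot be computed.** With no events in either arm it is 0/0. The probability is (1 − rate)^(2n). At 0.5% this is 0.995^300 = 22% or 0.995^350 = 17%. At 1% it is 5% or 3%.

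**3. Dependence on the approximation.** For a vs b events with n per arm and t = a + b, Pearson's statistic is X² = 2n(a − b)² / [t(2n − t)]. For 4 vs 0 at n=150:

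- X² = 300 × 16 / (4 × 296) = 4.05, p = 0.044.
- Fisher exact, two-sided: p = 0.12.

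For 5 vs 0 the two p-values are 0.024 and 0.060. The choice of test decides significance in both cases.

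**4. Exact size and power of the Pearson test.** These sum the product of the two binomial probabilities over all pairs (a, b) with Pearson p < 0.05, counting 0 vs 0 as no rejection.

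| True rates | n=150 | n=175 |
|---|---|---|
| 0.5% vs 0.5% (size) | 0.7% | 1.0% |
| 1% vs 1% (size) | 2.9% | 3.6% |
| 1% vs 2% | 9.3% | 10.5% |
| 0.5% vs 1.5% | 9.3% | 11.9% |
| 1% vs 3% | 21.5% | 24.6% |

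Under tripled harm, the chance of a non-significant result therefore runs from 1 − 0.246 = 75% to 1 − 0.093 = 91%.

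**5. What interval estimates could show.** With no events in an arm, the Clopper-Pearson 95% upper limit is 1 − 0.025^(1/n), which is 2.4% at 150 and 2.1% at 175. Newcombe 95% upper limits for the risk difference (published minus blinded), in percentage points:

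| Events, published vs blinded | n=150 | n=175 |
|---|---|---|
| 0 vs 0 | 2.5 | 2.1 |
| 1 vs 1 | 3.1 | 2.6 |
| 1 vs 0 | 3.7 | 3.2 |
| 2 vs 1 | 4.1 | 3.5 |

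The 0 vs 0 value is the Wilson upper limit z²/(n + z²) = 3.84/153.84 = 2.5 points at n=150.

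**The case against.** Several counter-arguments are fair.

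- **The test is not anti-conservative.** A reader might infer from the small counts that the test is invalid in the sense of raising false alarms. Step 4 shows the opposite. The approximation is poor, but exact size stays below 5% at the rates considered. This stands.
- **No rule equates non-significance with safety.** A reader might infer that p>0.05 will be taken as reassurance. The article does not say so. Its significance definition belongs to the primary efficacy analysis, and for borderline p-values there it asks for caution and emphasis on effect sizes. This stands. What remains is that the stated aim has no better-suited between-arm analysis behind it.
- **The event rate is borrowed.** The Introduction's figure is for neurosurgery in mild TBI generally, whereas the endpoint refers to intervention without that limit. This stands, and so the rate is labelled an assumption. The small-count problem nevertheless persists up to a rate of about 3%.
- **Safety does not rest on this test alone.** The Safety monitoring section provides prospective event capture, blinded adjudication and an independent Medical Monitor, and the 6- and 12-month calls look for delayed diagnoses. These improve ascertainment and oversight. They do not tell a reader how large an excess the data can exclude.
- **Interval methods and small-cell fallbacks usually belong in an SAP.** That would answer a complaint about missing detail. Here the article names a specific test, and that choice is the difficulty.
- **Fisher's test lowers power further.** For 1% vs 2% at 150 per arm it is 2.2%, against 9.3% for Pearson. This is correct, so merely exchanging one test for the other is not the remedy.

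**Conclusion.** The point holds as one that should be fixed. At assumed rates of 0.1–1%, about 0.15–1.75 events per arm are expected. The Pearson approximation is unreliable, and the comparison has 9–12% power for 0.5% vs 1.5% and 21–25% for 1% vs 3%. A non-significant result could not carry the Discussion's safety aim.

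Two stronger readings are not supported. Non-significance is likely under tripled harm (75–91%) but not nearly certain. Nor can one say in advance that the trial excludes an excess of 2–2.5 points: that holds only if neither arm has an event, which at equal rates has probability 17–22% at 0.5% and 3–5% at 1%. With one or two events per arm, the upper limit is about 2.6–4.1 points.

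The conclusions rest on the assumed event rate, 150–175 patients per arm and a two-sided 5% test. The primary analysis and the data collection are unaffected.

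**What to change.** In the Safety analysis section, replace the Pearson test for delayed diagnoses with:

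1. event counts and Clopper-Pearson 95% limits for each arm;
2. the risk difference with a score or exact 95% CI (Newcombe or Miettinen-Nurminen);
3. if a p-value is wanted, one from an exact test, labelled descriptive.

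State that safety will be interpreted by the upper confidence limit actually observed. Note that this limit is about 2.1–2.5 points even with no events, and about 2.6–4.1 points with one or two events per arm. Reword the sentence under Expected impact of the proposed trial so that safety is described and not concluded.

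This needs no further patients or data. The cost is a short text change and a more modest safety claim.
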